#### Acceptability of the telehealth intervention

Qualitative interviews are conducted during the intervention and via exit interviews asking about the participants’ experiences with telehealth, as well as the library and clinic staff’s experiences with delivering the library telehealth.Survey measures also measure the participants’ experiences with telehealth in general to see if changes occur over the course of the study.

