#### Feasibility of RCT to evaluate the current intervention

Rate of enrollment (Number of participants per week and per month).Proportion of interested and eligible participants who can successfully complete enrollment in the study.Study retention (proportion of RCT-enrolled participants who complete each follow-up assessment).Proportion of RCT-enrolled participants for whom outcome data are collected.We will track the proportion of participants who indicate willingness to be assigned to either condition (the percent of people who decline to participate because they do not like the randomization aspect of the study should be “none” to determine whether the study is feasible).

As a pilot study that is not statistically powered to assess efficacy, the study will provide effect size estimates of the library-facilitated telehealth BBB intervention on the primary outcomes, buprenorphine uptake and adherence, as measured by (1) presence of buprenorphine in weekly urine drug screenings at the library and at FJV health center, (2) buprenorphine prescription pick-ups, and (3) number and frequency of clinic visits, with secondary outcomes including use of fentanyl (e.g., illicitly manufactured) and other opioids (secondary outcome measured in weekly urine drug screens), and (4) self-reported substance use, mental health, and quality of life measures at 1-,2-,4-,8-, and 12-weeks, compared to a control group.

The control group will undergo the same procedures and receive the same incentives from the study staff in the library in terms of weekly assessments. They will also receive the same care from the clinic, except they will not be instructed to use the library telehealth option for their medical visits like the treatment group until their study participation is over. We hypothesize that patrons assigned to the library-facilitated telehealth group will uptake buprenorphine, pick up their buprenorphine prescriptions from the pharmacies, take buprenorphine after two weeks, and adhere to medical appointments more than the control (in-person clinic visits) group.

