### Pilot study design

This multisite study employs a parallel-arm randomized controlled trial design with participants allocated to library-facilitated telehealth visits for buprenorphine treatment (BBB intervention) or standard-of-care clinic-based or telephone visits (control). Participants are interviewed before randomization (baseline) and surveyed again at 1-, 2-, 4-, 8-, and 12-weeks (follow-up) to assess participant characteristics and study outcomes.

The study staff also conducts weekly urine drug screenings in the libraries with participants in both study arms to assess buprenorphine uptake and potential continued use of other drugs including fentanyl and other opioids. However, these additional urine drug screening and weekly follow ups at the library are not part of the usual clinic care or telehealth treatment procedures; instead, the clinic already requires in-person urinary drug screenings. Therefore, the additional library-based drug screenings occur to promote study engagement and retention in the study assessments, and to track outcomes without sole reliance on clinic record data. We also collect medical record and pharmacy pick-up data (via the CURES database described below) as part of the study design. Although these procedures are carefully determined to ensure rigor in the evaluation design, participating in these procedures is not a requirement for the library telehealth intervention itself. Participants can continue to use library telehealth without the need for weekly drug screenings in the library upon completion of the study.

Institutional Review Boards at San Diego State University and the University of California San Diego approved this study.

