### Data collection

#### Baseline and longitudinal assessments/measures

Following a FJV Health Center physician’s buprenorphine prescription, research staff track the participants’ buprenorphine medication uptake (pharmacy pickup, taking prescription one or more times during the first two weeks in the study), adherence (more than one buprenorphine positive screen), and medical appointment keeping through urinary drug screenings, interviews conducted at public libraries, and medical record data. All participants are invited to return to the library weekly for urinary drug screenings and to complete follow-up survey assessments at weeks 1, 2, 4, 8, and 12. Baseline and follow-up assessments are conducted in reserved library study rooms or conference rooms.

The 60-minute baseline survey captures the following domains: sociodemographic, behavioral, social supports, telehealth utilization and comfort, library usage, substance use behaviors, overdose experiences, and treatment history, along with the biomarker and medical record data collection (see Table 2). The content of the follow-up surveys is the same as the baseline surveys except that participant history and demographics are removed. The follow-up survey is shorter (30 min), retaining questions surrounding buprenorphine uptake, healthcare utilization, and barriers and facilitators to use. Follow-up questions also ask participants to recall experiences since their last visit with the research team in the library, particularly to determine the feasibility and acceptability of the library telehealth intervention; ease and understanding of being in the randomized controlled trial; experiences following up with the medical provider whether in-person or by telehealth; and their experiences with picking up and taking the buprenorphine medication.

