#### Sample size and planned data analyses

Our target sample size for the trial is 40 participants, although we allow for a maximum of 60 participants to account for attrition. The sample size will provide adequate precision for effect size estimates, though not statistically powered to assess efficacy on primary outcomes.

Buprenorphine uptake (the proportion who pick up and take buprenorphine at initiation, confirmed by CURES database pharmacy pickup records and urinary drug screenings) and adherence (taking buprenorphine > 1 time, ideally for 8 + weeks), medical appointment adherence (attended medical appointments for buprenorphine two or more times as confirmed by clinic medical record data) will be divided by the number prescribed and scheduled, respectively.

Adherence estimates from this study will also provide the basis for power calculations in the design of future efficacy trials. Quantitative data analysis will consist of univariate statistics to describe the entire study sample and by study arm, the prevalence of individual responses, and the prevalence of treatment uptake and adherence. We will conduct an intent-to-treat (i.e., per-randomization) analysis following CONSORT guidelines to explore potential differences between study arms on the outcomes. Specifically, we will use regression models testing each outcome separately (using the appropriate test depending on the outcome distribution, e.g., logistic regression with binary outcomes). These models will treat the intervention condition (library-facilitated telehealth intervention vs. treatment-as-usual control) as the exposure in unadjusted models.

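### The plan fixes unadjusted, arm-only models for secondary survey scores that are measured at baseline and five follow-ups, and so forgoes the baseline value and names no use of the repeated waves

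*Protocol article*

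**What the plan says.** **Data collected.** Pilot study design has participants interviewed before randomisation and "surveyed again at 1-, 2-, 4-, 8-, and 12-weeks (follow-up) to assess participant characteristics and study outcomes". The list of outcomes under Feasibility of RCT to evaluate the current intervention includes "self-reported substance use, mental health, and quality of life measures at 1-,2-,4-,8-, and 12-weeks, compared to a control group". The same measures exist at baseline: Baseline and longitudinal assessments/measures states that "The content of the follow-up surveys is the same as the baseline surveys except that participant history and demographics are removed", and Outcome ascertainment and post-intervention assessments lists baseline alongside the five follow-ups. Table 2 names the instruments, among them the NIDA-Modified ASSIST, AUDIT-C and PHQ-4. For experience with telehealth, the surveys are meant "to see if changes occur over the course of the study".

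**Analysis.** Sample size and planned data analyses gives one inferential method for all outcomes: "regression models testing each outcome separately", "using the appropriate test depending on the outcome distribution, e.g., logistic regression with binary outcomes", with the intervention condition "as the exposure in unadjusted models". The comparison is by randomised arm and is described as exploratory. The target is 40 participants, with up to 60 allowed for attrition. The section claims adequate precision for effect-size estimates but gives no interval width.

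**The concern.** For each survey score the trial will hold up to six values per person: one baseline and five follow-ups. The stated model has a single term, the arm. Two things follow from the wording.

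- The baseline value is left out. This is a stated choice, because the models are called unadjusted; an analysis plan that added baseline would depart from the published text.
- Nothing says which wave, or which combination of waves, is the outcome.

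Effect-size estimates are a stated product of this pilot, and the sample is small. A comparison at one wave without baseline gives wider intervals than the collected data allow. It also loses anyone absent at that visit, in a population where the article itself expects lost phones, displacement and attrition.

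**Working it through.** The article gives no standard deviation, correlation, alpha or interval width, so there is no figure of its own to reproduce. The check compares the variance of the estimated arm difference under different analyses of one continuous survey score.

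**Inputs**
- Follow-up waves k = 5, plus baseline (Pilot study design).
- N = 40, maximum 60 (Sample size and planned data analyses). Equal arms, so 20 or 30 each, is an assumption.
- Correlation ρ between any two of the six values: 0.3, 0.5 and 0.7, all assumed. The main check takes ρ equal for every pair and complete data.

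**Reference: one wave, unadjusted.** The 95% half-width in SD units is 1.96 × √(2/n). With n = 20 this is 1.96 × √0.10 = 0.62. With n = 30 it is 0.51.

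**Variance relative to that reference**
- One wave with baseline as covariate: 1 − ρ²
- Mean of five waves, no baseline: (1 + 4ρ)/5
- Mean of five waves with baseline: (1 + 4ρ)/5 − ρ²

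| Analysis | ρ = 0.3 | ρ = 0.5 | ρ = 0.7 |
|---|---|---|---|
| One wave + baseline | 0.91 | 0.75 | 0.51 |
| Five-wave mean, no baseline | 0.44 | 0.60 | 0.76 |
| Five-wave mean + baseline | 0.35 | 0.35 | 0.27 |
| Half-width of last row, N = 40 (SD) | 0.37 | 0.37 | 0.32 |

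**Reading the table**
- Baseline alone, at one wave: variance lower by 1 − 0.91 = 9%, 1 − 0.75 = 25% and 1 − 0.51 = 49%.
- Pooling alone: lower by 56%, 40% and 24%.
- Both: lower by 65%, 65% and 73%. The last formula peaks at ρ = 0.4, where 2.6/5 − 0.16 = 0.36, so over the whole range 0.3 to 0.7 the reduction is 64% to 73%. Interval width scales with the square root: √0.36 = 0.60 and √0.27 = 0.52, so intervals are 40% to 48% narrower.
- Like for like, for an analyst already using each person's five-wave mean: baseline changes 0.44 to 0.35, 0.60 to 0.35 and 0.76 to 0.27. These are reductions of 20%, 42% and 64%.

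**Check with decaying correlation.** Let ρ be the correlation at a 4-week gap, so that values t weeks apart correlate ρ^(t/4). The five-wave mean with baseline then has relative variance 0.304, 0.315 and 0.274, so 70%, 69% and 73% lower. For week 12 alone, the correlation with baseline is ρ³, and the relative variance with baseline is 1 − ρ⁶ = 0.999, 0.984 and 0.882. Under strong decay, baseline therefore helps a week-12 comparison little.

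These formulas ignore the small cost of estimating the baseline slope, which matters most at ρ = 0.3.

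**The case against.** The strongest case against has four parts.

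1. **The text is silent on waves rather than wrong about them.** This stands. In the quoted phrase, the word separately applies to outcomes. A reader might infer that the plan must either discard four waves or run five tests per score. The article states neither, and other options fit its wording: a per-person summary over waves, or GEE or a mixed model with arm as the exposure. A condensed article may leave the choice of wave to an analysis plan that is not shown. That does not cover the word unadjusted, which the article does state.
2. **The main outcomes are untouched.** This stands. Uptake is one yes/no result per person, and adherence already combines the weekly screens into one result. Appointment adherence is also a per-person summary. A reader might infer that the whole 40-person trial loses most of its precision; the point reaches only the repeated secondary scores.
3. **An unadjusted comparison is valid in a randomised trial.** This also stands. The loss is one of efficiency and involves no bias when data are complete.
4. **The gain depends on assumptions.** It rests on correlations that the article does not give, and the largest figures compare an average over follow-up with a single wave, which is a different estimand. With complete data, a week-12 estimand gains little from the other waves.

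Multiplicity adds little. If someone did test all five waves at an assumed 5%, the chance of at least one false positive would be 1 − 0.95⁵ = 22.6% for independent waves, and by simulation about 21%, 18% and 15% at ρ = 0.3, 0.5 and 0.7. But the article states no alpha, plans no such testing and calls the comparison exploratory.

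**Conclusion.** The point holds for the secondary self-reported scores and no further. The article commits to arm-only, unadjusted models for scores that have a baseline value and five follow-ups, and it names no use of the repeated waves.

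With assumed correlations of 0.3 to 0.7, adding baseline lowers the variance of a single-wave estimate by 9% to 49%. Where correlation decays with time, a week-12 estimate gains much less: 12% at most in the check above. For an average-over-follow-up estimand, five waves with baseline have a variance 64% to 73% below that of one unadjusted wave, with intervals 40% to 48% narrower. These figures assume a continuous score, equal arms and complete data. With missed visits, a model over all available waves would also retain people whom a single-wave analysis drops.

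The documents do not support saying that waves will be thrown away, that five tests per score are planned, or that the primary results are weakened. This is a worthwhile, low-cost improvement to a valid method.

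**What to change.** In Sample size and planned data analyses, for each repeated survey score:

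- Name one estimand, such as the arm difference at week 12 or averaged over the five follow-ups.
- Fit a mixed model, or GEE with small-sample standard errors, over all available waves, with arm, week, arm-by-week and the baseline value. Use the baseline survey completed before randomisation, as Pilot study design describes.
- State the missing-data assumption. A mixed model relies on missingness at random; unweighted GEE generally needs missingness completely at random.
- Keep the unadjusted comparison as a sensitivity analysis.

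The models for uptake and adherence need no change on this account. The cost is a few sentences and slightly more analysis work; data collection, procedures and sample size stay as they are. With about 20 people per arm, the model should be kept simple, and a per-person mean of the available follow-ups regressed on arm and baseline is a reasonable fallback for the average estimand if the full model does not converge.

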#### Timeline and dissemination plans

Results from the BBB study will be disseminated widely to organizational, clinic, and library partners, community networks, and nationally at substance use and library information science conferences in consultation with our community partners. Summary findings for community members (non-scientists) will be written following best practices for providing medical information to the public [61]. We will share results with our research partners and stakeholders (e.g., County) via open-access peer-reviewed publications, reports, news media outlets, and conference and community presentations. We aim to eliminate barriers to future Phase III efficacy trials by including residents, patients, providers, and libraries’ input before the study’s pilot. We intend to disseminate this information to these groups through such outlets.

Effect size estimates may also inform subsequent intervention research, including a fully powered efficacy trial, with this population and setting (see Fig. 1).

**Fig. 1 Fig1:**
[figure not shown]
Schedule of enrollment, interventions, and assessments*

## Discussion

This community-based randomized controlled trial pilot aims to improve buprenorphine uptake and adherence among persons with opioid disorders experiencing homelessness in San Diego County at a public space where they are at already- the public library. Co-created with two San Diego Public Libraries and Father Joe’s Villages’ federally qualified healthcare center, the pilot study attempts to demonstrate the library telehealth’s feasibility and acceptability among the unhoused library patrons with opioid use disorder, libraries, and the clinic staff.

### Conceptualizing each aspect of the intervention

In partnership with the researchers, the libraries adapt FJV Health Center’s free tele-buprenorphine treatment to their space using available resources to ensure its sustainability. Meeting rooms in the libraries, internet and library electronic device access, and a phone line in one library are available without additional costs or burden to the library beyond what they would ordinarily make available to the public. The two libraries are carefully selected after conducting interviews and focus groups at four libraries; two are selected for their on-site opioid overdose crises occurring and the easy proximal access to the clinic by foot or public transportation from their locations.

Both the libraries and clinic want the library telehealth intervention to continue without additional or continued cost once the research study ends. FJV Health Center and the researchers discuss procedures to minimize impact on the clinic staff, being intentional about following protocols already set in place by the clinic. The researchers’ study procedures for the sole purpose of data collection and tracking are not intentionally designed to be part of the sustainable intervention; only the library tele-buprenorphine via FJV is the intervention under study.

However, the research staff’s role at the library is similar to a social worker/case manager’s role that exists at some other U.S. libraries. In this case, the researchers help the participant navigate the steps of getting to the first medical appointment in-person to be enrolled in the study. In addition, they follow up with the participants and talk with them when conducting the interviews/surveys, which participants may perceive as an intervention in itself by virtue of interaction at a time in their lives when they have few others with whom to speak and be heard.

Requiring an in-person clinic visit prior to enrollment in the study was informed by shifting public policy. Federal legislation expanded physicians’ ability to initiate and maintain pharmacological treatment of opioid use disorder via telehealth (i.e., without an in-person medical evaluation) during the COVID-19 emergency “stay-at-home” public health policies. With mounting evidence supporting the use of telehealth and its benefits in reducing barriers to buprenorphine access, an extension to use telehealth instead of in-person clinic visitation was granted. Then, it was codified into permanent law [52].

As planning for our study continued, the federal regulation requiring at least one in-person visit was under debate. Because the clinic medical staff preferred to see the patients in-person before providing a prescription for buprenorphine for the first time, we will retain this as part of the study protocol even if laws shift to allow all virtual telehealth visits to be held without an in-person visit. We also stay with one clinic in order to not introduce other variables.

Though higher attrition may occur from screening to enrollment because of the in-person first clinic visit usual care and requirement, the full-scale future trial would adhere to this requirement because of the clinic’s standard practice to see a patient in-person for the first visit. The libraries’ proximity (walking distance or near to a trolley/public transportation stop) may introduce selection issues, excluding those without transportation passes or those unwilling to go to the downtown setting of the clinic. However, all participants in both control and intervention groups receive bus passes from the study. Both groups receive the same treatment by the research staff, library, and clinic so that we can attribute outcomes to the library telehealth intervention through a rigorous trial.

Enrolling participants only after they attend an in-person buprenorphine intake visit with a medical provider at the affiliated clinic may have implications for interpreting the feasibility data and generalizability. However, it is not possible to evaluate outcomes in this trial without this design decision if the goal is to have rigor through an RCT. This intentional design decision avoids enrolling participants who continue in the study for 12 weeks without ever seeing a medical provider as it would not allow us to detect the impact of the telehealth library intervention vs. usual in-person care.

### Impact of the intervention on the library

A challenge can be selecting an appropriate library with suitable infrastructure to allow for the study activities. Of four libraries we partnered with before conducting the RCT, we considered one in a mainly Latinx neighborhood of San Diego. However, we decide to cultivate the relationship with the community for future consideration instead because (1) the community surrounding the library is improving the area, and some focus group participants think the project may attract patrons who are not yet using the library in high numbers, (2) key informant community members say we would need to proceed carefully with participants who are not from the community who come to the library for the research study because they could become targets of territorial gangs. Therefore, another library could be a more practical choice, such as the ones we select for their high number of previous overdoses. For example, we choose to use one for its location above a riverbed, where many unhoused individuals stay, and its proximity to the public transportation trolley line.

### Strengths and limitations of the study design

Having drop-in clinic appointments available in both the telehealth library and in-person clinic control conditions is both a strength and limitation of the study. Drop-in appointments are a low barrier feature of the federally qualified healthcare center’s protocol that works well for unhoused patients. However, if a clinic setting does not allow drop-in clinic appointments, the implications are that a social worker in the library or health navigator will be even more necessary in real-world clinical practice to ensure patrons make and navigate their appointments on time. Usually, an appointment is made, but the clinic allows patients to see the medical provider within the block of time (i.e., morning or afternoon). If they do not show up at their appointment time, they can still see the medical provider within that morning or afternoon shift. Or, they can drop-in any other day on a first-come, first-serve basis. Generalizability is further limited by the requirement to have in-person visits for the first visit, though even during the COVID-19 pandemic when visits were mostly virtual, visits for in-person urine drug screenings were still required by FJV and other health centers.

Furthermore, if the rationale for the library-based intervention is to increase access to treatment, the frequency of urine tests and research assessments in this pilot study is greater than what is typically required in contemporary office-based buprenorphine treatment in many areasof the country. For this study, we want to have frequent follow-ups to ensure a higher likelihood of follow up to retain participants in the study protocols (surveys, interviews). However, an unintended consequence might be that participants will retain on buprenorphine more just by being in frequent contact with study staff. However, because we follow up weekly with all participants, regardless of the treatment vs. control condition, it does not impact our comparisons between conditions. An implication might be that having staff such as library social workers interacting with participants is important in carrying out such an intervention.

In addition, the twenty-dollar weekly incentive for the participants’ time doing follow-up assessments, although a moderate, non-coercive amount, may motivate their initial interest and retention in the study. However, the incentive should not have an effect on the uptake and retention of buprenorphine because participants do not receive any additional incentive for taking buprenorphine medication. The participants only receive incentives, including snacks/drinks and transportation passes, to compensate them for their time and travel to the study sites. Again, both the control and intervention group receive the same incentives. At the same time, incentives may be the key to engaging a hard-to-reach unhoused population into any kind of assistance in the first place.

Regarding treatment retention, pilot data would need to be interpreted with caution because social workers or library staff may not be available to assist the patrons with telehealth in the library afterwards or at other sites. However, overall, the study design attempts to enable library-facilitated telehealth to be sustained with minimal extra work for libraries and clinics. Some patrons might be able to do so more independently than others which would be interesting to study in itself. When planning for an efficacy trial, understanding determinants of successful implementation, including sustainability (and costs) of the treatment model will be taken into consideration for the full-scale trial.

